**Figure 1 figure1:**
[figure not shown]
Screenshot of daily stress and pain monitoring for the experimental group.

**Figure 2 figure2:**
[figure not shown]
Exemplar Feedback via Graphical Readout for Pain Intensity. YCWS: You Cope, We Support.

**Table 3 table3:** Description of You Cope, We Support banks of video links.

Study period and basic videos			Everyday videos		Favorite videos
**Short term**					
	A total of 6 video clips of guided relaxation and distraction exercises of various lengths: 2, 5, 8, 10, 15, and 20 minutes	Links to investigator-vetted relaxation and distraction exercises of various lengths that are freely available on YouTube		Initially, it will be an empty portfolio. Patients will store their favorite relaxation and distraction video links, which they can choose from basic videos and everyday videos.	
	Used all through week 1 to become familiar with the intervention and learn deep breathing exercise through instructions	Used during weeks 2-8		Used during weeks 2-8.	
	A total of 4 active components of the relaxation and distraction exercises: Soothing female voice Smoke images that change shape Deep breathing exercise Background sound	A total of 4 active components varied across two categories. Category 1: Either male or female voices Variety of nature images Background nature sounds Deep breathing exercise Category 2 Variety of nature images Background nature sounds No voice No deep breathing exercise		On the basis of patients’ preference. Investigators do not control the active components.	
**Long term**					
	Patients will continue to use video bank	Patients will continue to use video bank		Patients will continue to use video bank. Patients will have the ability to find their favorite video clips on the web and add them to favorite videos for personal use and recommend them via the investigators to the community of patients with sickle cell disease. Investigator will sequester and vet links that are not from basic videos and everyday videos to ascertain that they work and are valid before other patients can view them.	

Individuals can click on any of the 3 banks to choose a video to watch. The YCWS intervention can be customized by choosing video clips based on female or male voice, type of nature images, background sound, or lengths and by finding their own video clips. Patients can watch as many video clips as needed. Patients would be able to discern whether they received stress or pain relief after using the videos and determine which of the videos provided them with the most stress or pain relief. According to individual preference, we will send system-generated alerts or reminders to patients or a research staff will call, text, or email the patients to facilitate data entry and intervention use every 24 hours. The patient can also connect with our support staff about issues related to YCWS intervention use (experimental group only) and technical difficulties with study device or app for advice on what to do (both groups). Our support staff will monitor our database daily. If the patient does not enter data after 24 hours of system-generated alerts or reminders or messages via staff cell phone, the study support staff will contact them for data entry troubleshooting and, for the experimental group, for YCWS use as they indicated in their goals. During the short-term trial (weeks 1-8), patients will monitor their stress and pain daily, as described previously.

We will provide experimental group members access to 3 video banks from which they can choose their daily intervention. Patients will use only basic videos during week 1 to become familiar with the intervention and learn deep breathing and relaxation exercises through instructions. For example, one of the basic video clips entitled *Breathing out worry, breathing in light* guides the patients to “Notice the cloud-like formations on the screen. Observe how the images drift and change. As you breathe deeply, let your concerns and tensions (which worry you go) out into the atmosphere where they can dissolve just as the cloud-like formations on the screen dissolve and vanish from view. It is all right to let go of your worries. In fact, it is important to your health that you do so. Just breathe out problems and worries. See them drift off, walking by, and off the screen, no longer a part of you. Now, breathe in sunshine and healing energy.” This requirement is critical and supported by recent evidence showing that the respiratory control center communicates directly with and controls a brain center linked to attention, arousal, and panic [56]. [name] et al [57-60] ([name], unpublished data, January 2022) used these approaches in psychoneuroimmunology studies in patients with cancer or HIV, and we used them in our feasibility studies in patients with SCD. Some of the active components in the basic videos include colorful images similar to smoke or other nature images that slowly change shape against a dark background (images that do not represent any concept with known negative connotations), soothing female or male voice, deep breathing exercise, and slow-paced guided relaxation and distraction instructions. During weeks 2 to 8, patients will also have access to everyday videos and favorite videos.

During weeks 1 to 8, we will send system-generated alerts or reminders or messages every 24 hours to patients in the experimental group via phone call, text, or email to facilitate intervention use. If the patient does not enter data after 24 hours, the study support staff, who will be from the community or RS, will contact them 2 hours before the next data collection time for troubleshooting. The support staff will contact patients via chat, text, email, phone call, or FaceTime based on patients’ preferences to facilitate participation and troubleshoot. Owing to travel burdens including worsening of their pain in cold or hot weather, patient attendance in the monthly SCD support group is extremely low (1-2 patients per month). Patients with SCD report a preference for active remote support as opposed to face-to-face peer or social support because of weather, travel, and parking issues involved with receiving the support at an academic health center. Remote support also empowers them to participate in the study without the additional burden of traveling to the location of any peer or social support as recommended by the Chronic Disease Self-Management Program [61]. We specifically designed the support component of YCWS to incorporate the recommendations from our patient team members to address these issues and refine feedback messages and format.

During the long-term period (months 3-6), only system-generated alerts or reminders via messaging service or staff cell phone will be available. Patients will have the ability to find their favorite video clips on the web, add them to *favorite videos* for personal use, and recommend them via the investigators to other patients with SCD. We will vet these recommendations before releasing them to other patients. Throughout the study period, we will time stamp and track the patients’ YCWS web-based activities to capture data on system use.

#### Control Arm

The control arm includes self-monitoring of pain and stress, electronic monitoring of opioid use, and alerts or reminders. During the efficacy trial (weeks 1-8), similar to patients in the experimental group, patients will monitor their stress, pain, and opioid use daily. We will send system-generated alerts or reminders every 24 hours to patients via phone call, text, or email to facilitate data entry. If the patient does not enter the data after 24 hours of alerts or reminders, the study support staff will contact them for data entry troubleshooting. During the long-term period (months 3-6), patients will continue to self-monitor their daily stress and pain and use the electronic opioid use monitoring device. Patients will also continue to receive system-generated alerts or reminders via messaging service or staff cell phone. Throughout the study period, we will time stamp and track patients’ web-based activities to capture data on system use and outcome variables.

### Protocol Adherence Check for the Fidelity of the Control and YCWS Interventions

The PI will conduct reliability assessments for the RS’s implementation of the protocol on a random sample of 20% of the study measures. Although this assessment cannot be blinded, the RS will not be informed of the reliability check until the baseline data collection procedure is underway. If there are any deviations from the protocol, the RS will undergo additional training and supervised data collection to ensure protocol adherence.

### Intervention Fidelity

To improve fidelity, we will ensure that participants use the YCWS intervention as intended by monitoring the participants’ YCWS system use on the web. During the first 8 weeks, we will call or text participants 2 hours before the next data collection time if the patient does not enter data after 24 hours of system-generated alerts or reminders and has missed the period they indicated for completing the study, to encourage the use of YCWS. We will also ascertain if they are having trouble with accessing the program and will troubleshoot with the participants to resolve any issues. We will also monitor the participants’ self-monitoring of stress, pain, and opioid use in both groups. As a measure of intervention fidelity, the use of the system and measures will be documented by the app software that automatically writes time-stamped data to a SQL database. The fidelity of our pilot feasibility protocol is rigorous as the program is computerized and consistently implemented. In addition, we will monitor mobile device use, and time of use will be documented in the database to determine the intervention dose.

### Outcome Measures

#### Primary Outcome (Pain)

*Pain*, the primary outcome, will be measured using the pain intensity scale. This 3-item scale asks patients to report their current, least, and worst pain intensity in the past 24 hours on a scale of 0 (no pain) to 10 (pain as bad as it could be). We will calculate the average of the 3 scores to obtain an average pain intensity score, which has an internal consistency (*α*) of .85 [62] and predictive validity ([name], unpublished data, April 2022) in the population with SCD.

#### Secondary Outcomes (Stress and Opioid Use)

##### Stress

*Stress* will be measured using the stress intensity scale. This 3-item scale asks patients to report their current, least, and worst stress intensity in the past 24 hours on a scale of 0 (no stress) to 10 (stress as bad as it could be). We will calculate the average of the 3 scores to obtain an average stress intensity score. The internal consistency (*α*) of the stress intensity in the SCD sample was .82 [37]. It showed moderate, but not significant, correlation (*r*=0.41; *P*=.07) with the participants’ Perceived Stress Questionnaire (PSQ)-Recent score, demonstrating fair construct validity [37].

##### Opioid Use

We will use PAINReportIt [63-65] software program (Nursing Consult LLC) to collect data on drug names and doses of scheduled and as-needed opioid analgesics at baseline, and the data will be updated at week 8 and month 6. We will track opioid refills through patients’ pharmacies. We will use the Wisepill medication event monitoring system to collect data on opioid use. The Wisepill records the quantity of the medications. Each patient will receive 2 Wisepill devices, one for scheduled opioids and the other for as-needed opioids. The Wisepill medication event monitoring system was designed to monitor medication adherence and provide instant feedback via cellphone and internet technologies. The Wisepill has been used by patients with various health conditions, including tuberculosis [66], HIV [67], depression [68], and SCD [69]. The dispenser was designed such that it would be compelling and easy to use. It holds approximately 30 large pills or 60 small pills in a 7-compartment inner container and is powered by a 1100 mA lithium polymer rechargeable battery. We will use the Wisepill to record patients’ opioid use. Each week, the patient will fill the Wisepill with their scheduled and as-needed opioid medications on the day of the week indicated in their goals. Subsequently, patients will dispense their daily doses of medication from the Wisepill. Each time the compartment is opened, a cellular signal is sent and recorded in real time on a web-based server. The data are immediately accessible to the research staff for downloading via a secure internet interface. [name] et al [67] have used this device in previous studies.

#### Descriptive and Process Measures

##### PSQ-Recent

PSQ-Recent [70] is a 30-item tool that measures general perceived stress in the past week. The response options are 1 (almost never) to 4 (usually). Overall perceived stress index score is computed by subtracting 30 from the raw sum score and, then, dividing by 90, yielding scores that range from 0 to 1. High scores indicate great perceived stress. PSQ-Recent has demonstrated good test-retest reliability of 0.82 and good construct validity with the Perceived Stress Scale by Cohen (*r*=0.73) [70]. The internal consistency (*α*) reliability of the PSQ-Recent in our SCD sample was .94 [30]. We will collect these data to understand the context of our intervention.

##### System-Based Daily Activity

We will collect data on patients’ daily activities, such as the time spent on the YCWS intervention, including the time spent in using the video banks of RDE. The software will capture these activities by time-stamped data in the SQL database.

#### Demographic Characteristics

Questions regarding demographic characteristics and analgesics are also included in PAINReportIt [63-65]. Patients will report their age, sex, ethnicity, marital status, level of education, family income, weight, height, physical activity levels (per week), smoking status, stage in the menstrual cycle (women), previous use of computers, current access to computers, distance from care, and quality of internet connection. These data will be collected as composite demographic data to assess the participants’ representativeness and for prediction modeling.

#### Sickle Cell Self-efficacy Scale

The Sickle Cell Self-Efficacy Scale is a 9-item tool that measures patients’ beliefs in their ability to engage in daily activities despite having SCD and coping with obstacles or setbacks associated with SCD. For example, one of the items asks patients, “How sure are you that you can reduce your SCD pain by using methods other than taking extra pain medication?” The response options are 1 (not at all sure) to 4 (very sure). The total self-efficacy score is the sum of the 9 items, with scores ranging from 9 to 36. High scores indicate great self-efficacy. The Sickle Cell Self-Efficacy Scale has been validated in patients with SCD who are ≥11 years and has an internal consistency (*α*) of .87 in the population with SCD [71].

#### Study Acceptability Scale

Patients will also be asked to complete a 6-item questionnaire that focuses on the acceptability of the study [65]. Response options depend on the question. For example, the first question queries “Was participating in this study too hard?” The response choices are (1) not hard at all, (2) somewhat hard, and (3) too hard. This tool has been validated in the population with SCD in a study in which pen tablets were used [65] and in the preliminary study supporting this RCT. This scale provides data on the patients’ thoughts about the study processes and will help plan effectiveness or implementation studies.

#### Exit Interview Guide

This measure contains open-ended questions to solicit patients’ experiences with using a tablet for data collection (3 questions) and opinions (experimental group only) about the YCWS video clips and how they can be improved (3 questions). We will conduct an exit interview about staff support’s acceptability (1 question) and system-generated support (1 question). We will conduct the exit interview at week 8 (RCT-exit; short term) and month 6 (RCT-exit; long term). The exit interview will be audiotaped and transcribed verbatim. We used this measure in our feasibility study. We will use patients’ feedback to modify and improve our protocol for future studies.

### Data Collection and Management

The research data will be collected electronically using laptop and pen tablet computers. All the study surveys may be completed via the web using an app developed for this study. This application will contain PAINReportIt, a computer program developed by [name] to collect participants’ pain information and other surveys in electronic format. Participants’ data will be written directly to that server and will not reside, even temporarily, on the laptop or pen tablet computer. We will use HTTPS for encrypted data transfer to the College of Nursing server. The data will be stored in a secure College of Nursing server with access restricted to the immediate study personnel. All patients will be assigned a code number, and the research team will identify their data only with that code number. The link of the code numbers to the participant identifiers will be kept separate from the study data. Only the investigators and key personnel will have access to the code or master key. Any hard data collected will be stored in a locked office at the College of Nursing.

The software design will make every effort to reduce user errors; all data will be entered directly by the participant using an interface tested with cognitive interview methods that informed the final interface design. Consistency checks are built into the software so that inconsistent data (eg, out of range or logically inconsistent) are flagged immediately to inform the users and assess their intent. In addition, there will be more comprehensive consistency checks before data analysis. Inconsistent data points will be treated as missing. On the basis of our previous studies with this web application, we expect the percentage of inconsistent data values to be very low (<0.5%).

### Statistical Analysis

#### Overview

The study biostatistician will perform data management and analysis in collaboration with the PI and coinvestigators. The data will be stored in an SQL database and exported to the statistical software R for analysis. We will use an intention-to-treat approach, which includes all randomized participants in our analysis. We will consider *P*<.025 as statistically significant for intervention efficacy tests (short term and long term) on the primary outcome of pain intensity. For other inferences, we will consider *P*<.05 to be statistically significant. We will compute descriptive statistics (frequencies, means, SDs, etc) of baseline patient characteristics data, including demographics, pain, stress, and analgesic use before the test and compare the control group and the experimental group using chi-square tests or 2-tailed *t* tests. We expect no significant difference between the 2 randomly generated groups.

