**Methods:**

A randomized controlled trial of the short-term (8 weeks) and long-term (6 months) effects of YCWS on stress, pain, and opioid use will be conducted with 170 adults with SCD. Patients will be randomized based on 1:1 ratio (stratified on pain intensity [≤5 or >5]) to be either in the experimental (self-monitoring of outcomes, alerts or reminders, and use of YCWS [relaxation and distraction exercises and support]) or control (self-monitoring of outcomes and alerts or reminders) group. Patients will be asked to report outcomes daily. During weeks 1 to 8, patients in both groups will receive system-generated alerts or reminders via phone call, text, or email to facilitate data entry (both groups) and intervention use support (experimental). If the participant does not enter data after 24 hours, the study support staff will contact them for data entry troubleshooting (both groups) and YCWS use (experimental). We will time stamp and track patients’ web-based activities to understand the study context and conduct exit interviews on the acceptability of system-generated and staff support. This study was approved by our institutional review board.

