## Methods

### Study Design

The study is a randomized controlled trial (RCT) of the short-term (8 weeks) and long-term (6 months) effects of YCWS on efficacy outcomes (pain, stress, and opioid use), designed to determine the short-term and long-term effects of the YCWS intervention and to evaluate models that predict patient outcomes based on their group assignment and their personal and environmental characteristics.

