### Sample Size

For those who meet the eligibility criteria, we anticipate enrolling 195 participants to retain 170 (87.2%) participants with complete data at 8 weeks, based on a 13% attrition rate observed in our previous longitudinal studies in which follow-up was more than a year. We will strive for a sample in which 95% participants have African descent and approximately 50% are women. Our team has been exceptionally successful in conducting longitudinal studies using tablet technology with this vulnerable population and recruiting and retaining patients with SCD for pain research [16,47-50].

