#### Sample Power

The success of this study lies on its short-term and long-term efficacy on the primary outcome of pain intensity. We conservatively assume an SD of 3 for pain intensity based on values we observed in earlier studies. With a 2-sided type I error of 0.025, the proposed sample of 170 patients provides 80% power to detect a pain reduction of 1.5, below the minimal pain reduction of 2, which is considered as clinically meaningful.

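### A fixed P<.025 for each of the two primary pain tests is valid but more conservative than it needs to be; Holm's step-down rule keeps the same 5% familywise bound and can gain power

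*Protocol article*

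**What the plan says.** The Overview of the Statistical Analysis section sets the threshold for the two primary comparisons: P<.025 is taken "as statistically significant for intervention efficacy tests (short term and long term) on the primary outcome of pain intensity". All other inferences use P<.05. No ordering of the two tests, step-down or passing-on of alpha is described. The article does not name a familywise level; 5% follows from 2 × .025.

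Sample Power uses the same level ("With a 2-sided type I error of 0.025") and states that "the proposed sample of 170 patients provides 80% power to detect a pain reduction of 1.5", after "We conservatively assume an SD of 3 for pain intensity". It opens with "The success of this study lies on its short-term and long-term efficacy on the primary outcome of pain intensity". Study Aims and Hypotheses lists the short-term effect (first 8 weeks) and the long-term effect (months 3 to 6) as separate aims, each with its own hypothesis on pain.

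**The concern.** A fixed split holds the second test at .025 even when the first has been clearly rejected. At that point only one primary null hypothesis is left, and testing it at .05 would not take the familywise error above 5%. The article's rule leaves that room unused.

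In practice, a clear 8-week effect followed by a long-term P of .03 would have to be reported as no demonstrated long-term effect, although an equally strict rule would allow the claim. The long-term test is the more exposed one. Staff support is described for weeks 1–8 while months 3–6 keep only alerts or reminders (Interventions), and the retention target of 170 is stated for 8 weeks ("we anticipate enrolling 195 participants to retain 170 (87.2%) participants with complete data at 8 weeks"), so a smaller late effect or sample is plausible.

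**Working it through.** **Inputs.** From Sample Power: 170 patients, SD 3, difference 1.5, two-sided α = .025. From the abstract's Methods: "Patients will be randomized based on 1:1 ratio", hence 85 per arm. Assumed, because the article does not give it: the correlation ρ between the short-term and long-term test statistics, taken as 0.5 to 0.9, with 0 as an extreme. Also assumed: 85 per arm at both times.

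**1. The plan's own power figure.**
- SE = 3 × √(2/85) = 0.460.
- Expected z = 1.5/0.460 = 3.26.
- Critical value at two-sided .025 = 2.241.
- Power = Φ(3.26 − 2.241) = 84.6% (84.0% with the noncentral t).
- For 80% power: n per arm = 2 × 3² × (2.241 + 0.842)²/1.5² = 76.04, so 77 per arm, 154 in total.

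The stated 80% is therefore not reproduced exactly. It errs on the cautious side and does not affect the comparison below.

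**2. The two rules.**
- Fixed: reject each test if its P<.025.
- Holm: compare the smaller P with .025; if rejected, compare the other with .05 (critical value 1.960).

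Holm rejects everything the fixed rule rejects. It adds one case: one test has P<.025 and the other has P between .025 and .05. So P(both, Holm) = P(test 1 at .025 and test 2 at .05) + P(test 1 at .05 and test 2 at .025) − P(both at .025), evaluated with a bivariate normal distribution.

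**3. True difference 1.5 at both times.**

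| ρ | Each test, fixed → Holm | Both tests, fixed → Holm | At least one, either rule |
|---|---|---|---|
| 0 | 84.6% → 89.4% | 71.5% → 81.2% | 97.6% |
| 0.5 | 84.6% → 88.6% | 75.1% → 83.1% | 94.0% |
| 0.7 | 84.6% → 88.1% | 77.2% → 84.3% | 91.9% |
| 0.9 | 84.6% → 87.3% | 80.3% → 85.9% | 88.8% |

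Over ρ = 0.5 to 0.9, winning both gains about 6 to 8 points and each test about 3 to 4.

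**4. Other effect patterns (ρ = 0.5 to 0.9).**
- Short-term 1.5, long-term 1.0: expected long-term z = 1.0/0.460 = 2.17. Long-term power rises from 47.3% to 57.0–58.3%; short-term power goes from 84.6% to 84.6–85.9%.
- Short-term 1.5, long-term 0: short-term power goes from 84.6% to at most 84.7%. The long-term false-positive rate rises from 2.5% to 3.8–4.4%.
- Difference 2 at both times: each test goes from 98.2% to 98.8–99.0%, both tests from 96.8–97.5% to 98.4–98.6%.

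**5. Type I error with both nulls true.** Identical under the two rules: 4.9% (ρ = 0), 4.65% (0.5), 4.3% (0.7), 3.6% (0.9).

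**The case against.** The strongest reply is that nothing here is wrong. The threshold and the power calculation agree, familywise error is at most 5%, and choosing between two valid procedures is a matter of preference. The first part stands: a reader might infer an error or an inconsistency, and the article supports neither. What remains is that the article does fix a decision rule, and another rule with the same error bound rejects everything it rejects and sometimes more.

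A second reply is that the gain has a price, and this also stands. Simultaneous confidence intervals are less direct than the 97.5% intervals that match a fixed split. A short-term P between .025 and .05 stays undecided until the long-term test is known, whereas the fixed split judges each aim on its own data. When only one null is true, the chance of falsely rejecting it rises from 2.5% to about 4%. So Holm is not free in every respect, though these costs are small and the last stays under 5%. The article does not describe a separate early confirmatory claim at 8 weeks.

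Third, the size depends on the scenario. Each test gains only if the other is rejected. Sample Power regards SD 3 as conservative and takes 2 points as the clinically meaningful reduction; at that difference the gain nearly vanishes.

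Finally, a reader might infer from "The success of this study lies on its short-term and long-term efficacy on the primary outcome of pain intensity" that both tests must succeed, so that joint power is what counts. The sentence does not say so. If both were required for any claim, no split would be needed: testing each at .05 gives 83.7–87.3% power for both (ρ = 0.5 to 0.9), slightly above Holm. If either one suffices, Holm leaves the chance of success unchanged. Holm's benefit is clearest when the two aims are claimed separately, as Study Aims and Hypotheses sets them out.

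**Conclusion.** The point holds as a cheap efficiency improvement, not as the correction of an error. The fixed .025 for each test is valid and conservative.

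Under the plan's own inputs with a difference of 1.5 at both times, Holm adds about 6–8 points to the power for both tests and 3–4 points to each. It adds about 10 points to the long-term test if the late difference is 1.0 and the early one 1.5. It adds nothing to the chance of at least one success, next to nothing to one test when the other effect is zero, and at most 1–2 points at a true difference of 2.

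These sizes rest on 85 per arm at both times and on an assumed correlation of 0.5–0.9; fewer patients at 6 months would change them. The 5% familywise bound does not depend on the correlation. It would be too strong to say that power is gained for both tests in every case, or that a long-term P of .03 is called negative without reason: the reason is a prespecified control of multiplicity, only a stricter one than is needed.

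**What to change.** In the Overview of the Statistical Analysis section, replace the fixed threshold with: *The short-term and long-term pain tests are judged by the Holm procedure at a two-sided familywise 5% (the smaller P at .025; if rejected, the other at .05).* Settle this, with a date, before any unblinded comparison of outcomes. Keep the .025 power statement as the conservative planning case.

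State also whether trial success needs one or both tests. If both are required for any claim, each can be tested at .05 and neither Holm nor a split is needed.

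The cost is one or two sentences, with no extra patients, visits or data. The plan should accept that a short-term P between .025 and .05 waits for the long-term result. It should also say which confidence intervals will be reported; 97.5% intervals remain a simple conservative choice, although they can include zero where Holm rejects.
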